### Statistical methods

2.7

We will use chi-square test or Fisher exact test to compare the difference of the categorical variables between the groups with complete repair and with partial repair. The continuous variables will be compared between the two groups by Mann-Whitney *U* test. In order to exam the reliability of the outcomes of ultrasound elastography (including color histograms of each color and SWV), intraclass correlation coefficients (ICC) will be used to evaluate the inter-rater reliability and intra-rater reliability. When it comes to the correlational analysis of the findings of ultrasound elastography and MRI, Spearman's rank correlation is used for 2 continuous variables, while Cramer's V correlation is used for one continuous variable versus one nominal variable. The predictive validity of ultrasound elastography for the reparability of large-to-massive RCTs will be analyzed by receiver operating characteristic (ROC) analysis to calculate the area under the curve (AUC). Finally, we will perform a logistic regression for the associations between the reparability and risk factors (such as age, sex, body mass index (BMI), inflammatory arthritis, the findings of ultrasound elastography, the findings of MRI). The statistical analysis will be performed using Stata 15 (StataCorp. 2017. Stata Statistical Software: Release 15. College Station, TX: StataCorp LLC.). A *P* value less than .05 will be defined as statistically significant.

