### Sample size estimation

2.8

The sample size estimation for a ROC analysis will based on a research by Hanley et al.^[23]^ According to Iagulli et al,^[24]^ about half of large-to-massive RCTs can be completely repaired, so the ratio of partial repair cases to complete repair cases is supposed to be 1. Under the assumption of (1) type I error = 0.05 (2) type II error = 0.2 (3) acceptable discrimination is 0.7, the sample size should be 62 participants. The estimated sample size will be corrected to 78 participants in consideration of 20% drop-out rate.

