## Discussion

3

In this study, we will inspect the reliability of ultrasound elastography when applied for preoperative evaluation of large-to-massive RCTs. The relationships between the findings of ultrasound elastography and MRI will also be examined. The degree of muscle atrophy and fatty infiltration of large-to-massive RCTs is more severe than other types of rotator cuff injury. Because the previous study by Rosskopf et al^[16]^ did not focus on the subgroups of large-to-massive RCTs, our study can confirm the application of ultrasound elastography in such cases. Besides, further ROC analysis and logistic regressions can help us to build a predictive model for reparability of large-to-massive RCTs preoperatively. Although similar study had been done by MRI,^[14]^ our study used ultrasound elastography to construct the predictive model for the sake of better availability than MRI. The outcomes of this study may help the clinicians for the preoperative prepare.

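### The study is sized for a single AUC (about 31 partial repairs), but the regression meant to feed a predictive model draws on an open list of 6 to about 22 terms, so its apparent performance is likely to be clearly optimistic

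*Protocol article*

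**What the plan says.** Statistical methods (2.7) of the protocol article ends its analyses with: "Finally, we will perform a logistic regression for the associations between the reparability and risk factors". The examples that follow are age, sex, BMI, inflammatory arthritis, the elastography findings and the MRI findings. The list is illustrative, and the last two entries are groups of measures, not single variables.

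The Discussion gives these regressions a predictive purpose: together with the ROC analysis, "logistic regressions can help us to build a predictive model for reparability of large-to-massive RCTs preoperatively".

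Sample size estimation (2.8) addresses a ROC analysis only. It assumes that "the ratio of partial repair cases to complete repair cases is supposed to be 1", with "type I error = 0.05", "type II error = 0.2" and "acceptable discrimination is 0.7". It concludes that "the sample size should be 62 participants", and then: "The estimated sample size will be corrected to 78 participants in consideration of 20% drop-out rate".

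The Image section (2.5.2.1) defines the available measures:
- Compression elastography: three colours in each of two muscles.
- Shear wave velocity: one mean for each of four quadrants in each of two muscles.
- MRI: tear size, Patte grade, Goutallier grade and tangent sign.

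**The concern.** Three things fixed in the article do not fit together: a sample chosen for one AUC, a predictor list with no upper limit, and a predictive aim. In a logistic model the information is governed by the smaller outcome group, here about 31 patients. When many coefficients are estimated from so few events, part of the apparent discrimination is fitted noise, the odds ratios become extreme, and complete separation can occur.

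The Discussion hopes the results will help clinicians prepare for surgery. If the AUC from the fitting data were reported as the model's performance, surgeons could be given a tool that ranks new patients much less well than stated and whose predicted probabilities are too extreme.

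**Working it through.** **1. The plan's own sample size.** The inputs from section 2.8 are alpha 0.05, power 80%, AUC 0.7 and ratio 1. A null AUC of 0.5 and a two-sided test are assumptions, because the article states neither. The Hanley-McNeil variance term is V(A) = Q1 + Q2 − 2A², with Q1 = A/(2 − A) and Q2 = 2A²/(1 + A).

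- V(0.5) = 0.3333 + 0.3333 − 0.5 = 0.1667, square root 0.408.
- V(0.7) = 0.5385 + 0.5765 − 0.98 = 0.1349, square root 0.367.
- n per group = ((1.96 × 0.408 + 0.842 × 0.367)/0.2)² = 30.76, so 31 per group and 62 in total.
- Dropout: 62/0.8 = 77.5, so 78.

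Both stated figures reproduce. The calculation makes no allowance for a multivariable model.

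**2. Events.** 62 patients at 1:1 give 31 partial repairs. If all 78 were evaluable there would be 39. Any departure from 1:1 makes the smaller group smaller still.

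**3. Possible term counts.** The article fixes no term list, so the count is a range.

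| Reading | Terms | Events per term (31 events) |
|---|---|---|
| One term per named factor or group | 6 | 31/6 = 5.2 |
| 4 clinical + 2 velocity means (one per muscle) + 4 MRI, no colours | 10 | 31/10 = 3.1 |
| As above, plus 3 colours × 2 muscles | 16 | 31/16 = 1.9 |
| 4 clinical + 6 colour + 8 quadrant velocities + 4 MRI | 22 | 31/22 = 1.4 |

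Dummy-coded grades, or Goutallier grades per muscle, would push the last row above 22. With 39 events, 22 terms give 39/22 = 1.8.

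**4. Expected shrinkage.** A true AUC of 0.7 at 1:1 corresponds to a Cox-Snell R² of about 0.121. At n = 62 the model chi-square is −62 × ln(1 − 0.121) = 8.0, and expected shrinkage is 8.0/(8.0 + p):

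- 6 terms: 8.0/14.0 = 0.57.
- 10 terms: 8.0/18.0 = 0.44.
- 22 terms: 8.0/30.0 = 0.27.

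The sample size for a shrinkage of 0.9 is n = p/((0.9 − 1) × ln(1 − 0.121/0.9)). With 22 terms this is about 1,520. It is proportional to p, so 6 terms need about 1,520 × 6/22 = 415.

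**5. Simulation.** Unpenalised logistic regression was fitted to 31 v 31 patients with independent normal predictors, then tested on 2,000 new patients.

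| Terms | True AUC | Apparent AUC | AUC in new patients |
|---|---|---|---|
| 6 | 0.70 | 0.76 | 0.65 |
| 10 | 0.70 | 0.80 | 0.63 |
| 22 | 0.70 | 0.90 | 0.58 |
| 6 | 0.80 | 0.84 | 0.76 |
| 22 | 0.80 | 0.95 | 0.67 |
| 22 | 0.50 (no signal) | 0.86 | 0.50 |

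With 22 terms at a true AUC of 0.70, the calibration slope in new patients was about 0.08, and complete separation occurred in about 8% of runs. The result does not depend on how the signal is spread: 22 terms give about 0.90 v 0.58 with all signal in one predictor and 0.91 v 0.58 with it spread over four. With 39 per group, 22 terms still give 0.86 v 0.60.

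**The case against.** The strongest objection is that the article does not describe a 22-term model. The Image section says what is measured, not what enters the regression. Quadrants may be averaged, measures may be selected, and the Discussion speaks of regressions in the plural, which fits several small models. This stands. A reader might infer that at least 22 terms will be fitted together, but the document supports only a range starting at six.

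A second objection is that penalisation and internal validation are commonly left to a full protocol or analysis plan, and neither is shown. This also stands. A reader might infer that the sponsor has chosen unpenalised fitting without optimism correction, but the article is merely silent. The point rests on what the article does state: the sample size basis, the open list and the predictive aim.

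Third, section 2.7 calls the regression one of associations, and the Discussion prefers ultrasound because it is more available than MRI, so MRI terms may not belong in the predictive model. That is a fair reading. It supports separating the two purposes explicitly, since section 2.7 now puts both sets of findings into one list.

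Fourth, the primary analysis is the ROC analysis, and its sample size reproduces. Correct, and this limits the severity. The objection does not remove the point, because even the six-term reading shows a gap of about 0.11 in AUC (0.76 − 0.65) at a true AUC of 0.70.

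**Conclusion.** The concern holds for the secondary predictive model, at moderate severity. With about 31 partial repairs, the apparent AUC is likely to exceed performance in new patients by about 0.11 with 6 terms, 0.17 with 10 (0.80 − 0.63) and 0.32 with 22 (0.90 − 0.58), if the true AUC is 0.70. With a stronger true signal of 0.80 and 6 terms the gap is about 0.08 (0.84 − 0.76), milder but still present.

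A reader might go further and conclude that the model is bound to look excellent and fail. The documents do not support that certainty, because the outcome depends on the terms fitted, the fitting method and the true signal. Nor is the primary analysis undermined: a ROC curve for one elastography measure fixed in advance has no fitted coefficients to overfit.

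The figures assume a 1:1 split, 62 evaluable patients, unpenalised fitting and independent normal predictors. Correlation among colours and quadrants would change the exact values. With no signal it made almost no difference: 22 terms gave an apparent AUC of about 0.86 at within-block correlations of 0, 0.5 and 0.8, against 0.50 in new patients.

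**What to change.** In Statistical methods (2.7), separate the predictive model from the association analyses:

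- Name in advance a short list of terms for the predictive model, for example one summary elastography index and a few clinical factors. The exact number is a judgement. Even 4 terms gave 0.74 v 0.67 at a true AUC of 0.70, so a short list reduces optimism without removing it.
- Fit the model with Firth or ridge penalisation.
- Report the bootstrap optimism-corrected AUC and the calibration slope as its performance, repeating every modelling step within each bootstrap sample.
- Keep the wider adjusted associations, including those with MRI findings, but label them exploratory.

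If a full protocol or analysis plan already provides for this, a sentence saying so is enough. The cost is some wording, a modest amount of extra analysis and a lower reported AUC for the multivariable model. No extra patients or measurements are needed, and the primary single-measure ROC analysis is unchanged.

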### Sample size estimation

2.8

The sample size estimation for a ROC analysis will based on a research by Hanley et al.^[23]^ According to Iagulli et al,^[24]^ about half of large-to-massive RCTs can be completely repaired, so the ratio of partial repair cases to complete repair cases is supposed to be 1. Under the assumption of (1) type I error = 0.05 (2) type II error = 0.2 (3) acceptable discrimination is 0.7, the sample size should be 62 participants. The estimated sample size will be corrected to 78 participants in consideration of 20% drop-out rate.

## Discussion

3

In this study, we will inspect the reliability of ultrasound elastography when applied for preoperative evaluation of large-to-massive RCTs. The relationships between the findings of ultrasound elastography and MRI will also be examined. The degree of muscle atrophy and fatty infiltration of large-to-massive RCTs is more severe than other types of rotator cuff injury. Because the previous study by Rosskopf et al^[16]^ did not focus on the subgroups of large-to-massive RCTs, our study can confirm the application of ultrasound elastography in such cases. Besides, further ROC analysis and logistic regressions can help us to build a predictive model for reparability of large-to-massive RCTs preoperatively. Although similar study had been done by MRI,^[14]^ our study used ultrasound elastography to construct the predictive model for the sake of better availability than MRI. The outcomes of this study may help the clinicians for the preoperative prepare.
